### Study recruitment and selection

The clinical trial started in January 2016, suspended in January 2017 due to relocation of the Principal Investigator’s laboratory and re-started in January 2019. We maintain an interprofessional recruitment team that resides at Spaulding Rehabilitation Hospital. The recruitment team consists of the site principal investigator, a clinical trial coordinator, research assistants, postdoctoral research fellows, as well as, onsite physicians and research physical therapists.

We also have a Medical and Data Monitor to assess participants for significant adverse events, to assess for data integrity issues during the trial, and to determine if an adverse event requires reporting to the Principal Investigator, IRB, and Department of Defense and report integrity findings and recommendations to the Principal Investigator.

Our team realizes that recruitment is a critical component to the success of this clinical trial and is of highest priority. We established an Institutional Review Board (IRB)-approved recruitment strategy to permit a broad range of methods to recruit potential participants in our trial. This includes patient registries, site-specific clinical research networks (e.g., Spinal Cord Injury Model System, SCIMS), novel internet-based advertisement (e.g., Facebook), and website inquiry forms. We post recruitment information on relevant forums such as Spaulding’s Partners Rally, CenterWatch, and ClinicalTrials.gov and paper flyers at Spaulding Rehabilitation Hospital. Our team clinicians also review, on a daily basis, SCI diagnosis (confirmed by ICD-10 codes), demographics, and co-morbidities of patients admitted to our clinical sites. To avoid bias or coercion in the recruitment process, the team follows a written script to communicate with persons who contact us with interest in the study or whom we identify from these recruitment sources.
A.Inclusion and exclusion criteria

If the person meets our initial screening requirements, the study coordinator schedules the person for an on-site assessment to determine if they meet all inclusion and exclusion criteria (Table 1). Due to the timing of this intervention study, we anticipate that eligible participants receive ongoing rehabilitation services. We do not exclude persons from this study if they are receiving gait rehabilitation provided the treatments are not during our 2-week intervention. We do exclude persons with severe sleep-disordered breathing. To evaluate this possibility, potential participants complete one night of sleep with a portable pulse oximeter [ApneaLink®, Nonin Inc. USA]. This unit records up to 10 continuous hours of heart rate (HR), respiration rate (RR), and oxygen saturation (SpO_2_) [25]. We exclude individuals with scores of > 30 apneas and hypopneas per hour indicative of OSA [23, 26] and recommend they seek further evaluation from a certified sleep specialist.

**Table 1 Tab1:**
[figure not shown]
Study eligibility criteria

Since we do not yet know of any differences in responsiveness to daily AIH according to the gender or race of persons with SCI [27], we will balance our recruitment across testing groups (Aims 1 and 2) based on age, gender, and race. However, to protect against possible side effects of daily AIH, women who are pregnant or nursing a child may not take part in this study, as the effects of daily AIH on the developing fetus or infant have not been studied.
B.Informed consent process

Potential participants must read and sign the study’s consent form and Health Insurance Portability and Accountability Act (HIPAA) waiver prior to study enrollment. Our consent form incorporates the International Campaign for Cures of Spinal Cord Injury Paralysis inclusion and exclusion criteria recommendations to account for ethical considerations, safety, and potential confounds during participant recruitment [28]. Potential participants who sign the consent form undergo a medical screen by one of the study physicians and a physical screen by one of the study physical therapists. The medical screen ensures the participant meets all inclusion criteria and has no underlying medical conditions that may make them ineligible to participate. During the physical screen, the team physical therapist evaluates the individual’s functional walking ability, strength, spasticity, and pain levels using standardized clinical assessments that have high inter-rater reliability.

#### Randomization and stratification

We stratify eligible participants into either an ambulatory or a non-ambulatory group based on their initial walking function. The ambulatory group includes eligible participants who successfully complete one of the following without human assistance: TUG, 10MWT, or 6MWT without human assistance. Participants enrolled in the non-ambulatory group are unable to complete any of these assessments at initial screening. Prior to enrollment of the first study participant, a research statistician generated the balanced, randomization scheme for treatment allocation in both non-ambulatory and ambulatory groups using the R Statistical Package [29]. Using this scheme, the clinical coordinator assigns each participant to their respective treatment group using their alphanumeric identifier.

Although we inform participants about their group, we blind them to the treatment they receive (i.e. daily AIH or daily SHAM). The clinical raters, trainers, and data analysts are also unaware of the treatment that each participant receives during after the trial. We plan to rigorously quantify our blinding methods. Participants guess the breathing intervention received at the end of each treatment day and indicate guess confidence using a Likert scale [30, 31]. Using a contingency table and Fischer’s Exact Test, we will determine if the probability of correct guessing is different from chance. Using multivariate logistic regressions, we also will assess factors that may influence guessing (e.g., adverse events, perceived effects, and sensorimotor changes).

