
### Outcome measures

We provide a summary of primary and secondary outcomes measures in Table 3. We quantify overground walking ability using three primary measures: timed up-and-go test (TUG, walking initiation and balance), ten-meter walk test (10MWT, walking speed), and six-minute walk test (6MWT, walking endurance). These tests capture functional ambulation, exhibit high reliability and construct validity, and have precedence for quantifying and distinguishing degrees of functional ambulatory recovery post SCI [38–40]. In our previous study in persons with chronic SCI, we found these tests to be more sensitive to changes in walking function and functional ambulation compared to AIS grade or categorical ambulation metrics [41]. During all walking assessments, we use a 75-ft long walkway and allow participants to use their least restrictive hand-held assistive device of choice (if needed).

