**Table 3 Tab3:**
[figure not shown]
Timeline for clinical assessments and outcome measurements

We ensure a minimum of 5-min for rest breaks between tests. Participants able to ambulate attempt two trials each for the TUG and 10MWT (at their fastest, but comfortable and safe speed) with a minimum of 1-min rest between trials. The average TUG time and 10MWT speed for the two the trials will be used for analyses. Participants will attempt a single trial of the 6MWT at their fastest yet comfortable walking speed that is sustainable for six minutes, while distance covered at 2 and 6-min time points is recorded. We quantify success of completing each of the tests using a recovery score of 0–3 (0 = complete, 1 = attempted test, 2 = partially recovered but failed to complete; 3 = fully recovered). We also record secondary outcome measures of walking function that include the Walking Index for Spinal Cord Injury (WISCI) II [42] and SCI Functional Ambulation Index (SCI-FAI) [43].

To quantify maladaptive changes that may potentially occur following daily AIH exposure, we measure the magnitude and frequency of pain, spasticity, systemic hypertension, and autonomic dysreflexia during our assessments.

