### Statistical analysis

To advance our understanding and the applicability of daily AIH-induced walking recovery, we plan to test three sub-hypotheses using parametric and non-parametric statistical inferencing. Statistical significance corresponds to a p-value less than 0.05.

#### Hypothesis 1

Daily AIH improves walking recovery in persons with subacute SCI initially unable to walk as compared to daily SHAM. We plan to quantify the success of completing walking skills using our primary outcome measures (i.e., TUG, 10MWT, and 6MWT) by a recovery score of 0–3. We predict that the number of walking skills recovered will be greater for participants receiving daily AIH vs daily SHAM, indicating improved walking ability. We will use a Friedman two-way (factor 1 = intervention: daily AIH, daily SHAM; factor 2 = time: baseline, mid-test, post-test, and follow-ups) repeated measures analysis of variance (ANOVA) by ranks to compare walking recovery between and within groups. If there are significant differences, we plan post-hoc tests for pairwise comparisons [50]. We also anticipate that improvement in walking recovery will correlate with improved SCI-FAI, WISCI and LEMS scores, suggesting clinical relevance of daily AIH as an intervention across various SCI impairment levels.

#### Hypothesis 2

Daily AIH + WALK improves walking ability in ambulatory persons with subacute SCI as compared to daily SHAM+WALK and WALK. We predict a decrease in 10MWT and TUG time and an increase in 6MWT distance relative to baseline following dAIH+WALK (vs. dSHAM+WALK, WALK). We will test three related sub-hypotheses using a linear mixed model with fixed effects [51]. We will use intervention (daily AIH + WALK, daily SHAM+WALK, WALK) and time (day) as the fixed main effects, with subject as random effect, while scores for TUG (time), 10MWT (time), and 6MWT (distance) will be considered as repeated measures. Differences from baseline scores will be compared between and within interventions at mid-test, post-test, and follow-ups. If ANOVAs reveal significant differences, we will use the Tukey-Kramer post-hoc test to identify pairwise differences. If baseline measures are significantly different between intervention groups, we plan to use an analysis of co-variance (ANCOVA) to analyze these data.

#### Hypothesis 3

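### The 10MWT, a primary outcome, is analysed as speed in one section and as time in another, and the time scale has no value for ambulatory-group participants who cannot complete the test

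*Protocol article*

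**What the plan says.** **Scale of the 10MWT.** The Abstract names the 10MWT as the measure of overground walking speed. The Outcome measures section lists it among the three primary measures as "ten-meter walk test (10MWT, walking speed". The text after Table 3 then fixes the analysis variable: "The average TUG time and 10MWT speed for the two the trials will be used for analyses". Under Statistical analysis, Hypothesis 2, the scale changes: "scores for TUG (time), 10MWT (time), and 6MWT (distance) will be considered as repeated measures". The prediction there follows the time scale: "We predict a decrease in 10MWT and TUG time and an increase in 6MWT distance relative to baseline".

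**Who enters Aim 2.** Under Randomization and stratification, "The ambulatory group includes eligible participants who successfully complete one of the following without human assistance: TUG, 10MWT, or 6MWT". The other group is the complement: "Participants enrolled in the non-ambulatory group are unable to complete any of these assessments at initial screening". One completed test out of three is therefore enough for Aim 2.

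**What is compared.** For Hypothesis 2, "Differences from baseline scores will be compared between and within interventions at mid-test, post-test, and follow-ups". If baseline differs significantly between arms, an ANCOVA is to be used.

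**Non-completion.** A 0–3 recovery score is defined for each of the tests, but the Statistical analysis section uses it only under Hypothesis 1. The rule under Intervention, Duration, for recording data as missing concerns a missed assessment session, not a test that was tried and not completed. For the 6MWT, "distance covered at 2 and 6-min time points is recorded".

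**The concern.** The two statements about the 10MWT cannot both be followed. Each names the quantity to be analysed, so this is more than loose wording, and the result for a primary outcome could depend on which section the analyst follows.

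The time scale raises a second difficulty. A participant who enters the ambulatory group on one test alone may be unable to complete the 10MWT or the TUG. No finite time then exists at baseline, and a difference from baseline on that test is undefined. The same gap opens at a later visit if ability is lost. These values are missing because of walking ability, which is what the trial measures, so treating them as ordinary missing data could bias the comparison of arms. The document does not settle the direction of that bias. On the speed scale inability has a natural value, 0 m/s; on the time scale it has none. The two difficulties are therefore linked.

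**Working it through.** The plan gives no figure on this point to reproduce. The check is arithmetic on the two scales, followed by a comparison of the entry rule with the analysis. The walking speeds and trial times below are illustrative, because the article gives no baseline speed distribution.

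**1. Same gain, two scales.** Time over 10 m is 10/speed.
- From 0.1 to 0.2 m/s: 10/0.1 − 10/0.2 = 100 − 50 = 50 s.
- From 1.0 to 1.1 m/s: 10/1.0 − 10/1.1 = 10 − 9.09 = 0.91 s.
- Ratio: 50/0.91 ≈ 55.

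The pattern does not depend on those two speeds. A gain of 0.05 m/s shortens the time by 33.3 s from 0.1 m/s, 10.0 s from 0.2 m/s, 1.8 s from 0.5 m/s and 0.5 s from 1.0 m/s. Mean change in time is therefore driven by the slowest walkers.

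**2. The order of improvement can reverse.**
- Participant A goes from 0.10 to 0.12 m/s: gain 0.02 m/s; time saved 100 − 83.3 = 16.7 s.
- Participant B goes from 1.0 to 1.3 m/s: gain 0.3 m/s; time saved 10 − 7.7 = 2.3 s.

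Time ranks A as the larger improvement and speed ranks B.

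**3. Averaging two trials.** This is a smaller effect.
- Trials of 40 s and 60 s: mean speed (0.250 + 0.167)/2 = 0.208 m/s; speed at the mean time 10/50 = 0.200 m/s, a difference of about 4%.
- Trials of 60 s and 100 s: 0.133 against 10/80 = 0.125 m/s, about 7%.

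**4. Entry rule against analysis**, for an ambulatory-group participant who has not completed the test at baseline:

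| Test | Scale under Hypothesis 2 | Baseline value |
|---|---|---|
| TUG | time | none that is finite |
| 10MWT | time | none that is finite |
| 10MWT | speed, as in Outcome measures | 0 m/s is available |
| 6MWT | distance | a partial or 2-minute distance can exist |

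**5. How much could be lost.** The article does not say what share q of Aim 2 participants would lack a baseline time, so q is an assumption. With 51 participants, 12% attrition and three arms, 51 × 0.88/3 ≈ 15 per arm are evaluable. No Aim 2 effect is planned for the 10MWT, so the standardised 6MWT effect is borrowed: 100 m/90 m = 1.11. A two-sided t-test at 0.05 then has power 0.836 at q = 0, 0.79 at 10%, 0.74 at 20% and 0.68 at 30%. This holds only if those participants leave the comparison altogether, and it measures lost precision, not bias.

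**The case against.** The strongest reply is that the document is a condensed article. How a failed test is scored is normally left to the full protocol or the SAP, and neither is shown. That stands: the absence of a scoring rule is not itself an error. The contradiction between speed and time is of a different kind, because both statements are in the article and no further document can make both true.

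A reader might infer more than the article supports:

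- *That all three primary outcomes lack a baseline value for weak walkers.* The 6MWT is analysed as distance, and distance is also recorded at 2 minutes, so a participant who stops early can still have a value. The Aim 2 sample size rests on this outcome.
- *That such participants drop out of Aim 2.* The mixed model keeps observed visits, and the comparison of differences from baseline could be read as contrasts within the model. A participant is lost only for the outcome or visit without a value. A missing baseline removes them from that outcome if change scores are the response or baseline is a covariate.
- *That a known share of the sample is lost.* No figure is given.
- *That TUG should also move to a reciprocal scale.* The Outcome measures and Statistical analysis sections agree on TUG time, so changing it would be a preference.

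It can also be said that the 55-fold ratio compares two chosen extremes. That is fair, but the weighting towards slow walkers follows from the reciprocal and appears across the whole range in step 1. Finally, redefining a primary outcome in a trial that began in 2016 is not trivial. Here, though, speed is already the scale in the Abstract and the Outcome measures section, so the change reconciles the text with what is stated elsewhere.

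**Conclusion.** The point holds in two linked parts. First, the article contradicts itself on the analysis variable for the 10MWT: averaged speed in Outcome measures, time with a predicted decrease under Hypothesis 2. The scales are reciprocal and weight the same gain up to 55-fold differently between 0.1 and 1.0 m/s, so a primary result can differ with the section followed. This part needs no assumption beyond the arithmetic.

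Second, the one-test entry rule admits participants who can have no finite baseline 10MWT or TUG time, while the analysis compares differences from baseline. Gaps of this kind are informative. Their number cannot be derived from the article, and the power figures above are illustrations over an assumed range. The effect is confined to the affected outcome and visit, with 6MWT distance least exposed. Using speed for the 10MWT resolves the first part and gives that test a usable value for inability.

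**What to change.** In Statistical analysis, Hypothesis 2:

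1. Replace 10MWT time with 10MWT speed in m/s, averaged over the two trials as Outcome measures already says, and change the prediction to an increase in speed.
2. Score inability to complete the 10MWT as 0 m/s at every visit, including baseline. Keep this distinct from a missed assessment session, which stays missing.
3. Keep TUG as time.
4. Add a rank-based sensitivity analysis for TUG and 10MWT in which inability takes the worst rank.

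The cost is a dated change of wording; no new data are needed. The downside is a cluster of 10MWT values at zero, which a linear mixed model handles imperfectly and which the rank analysis addresses. The change should be made and recorded before unblinding, so that the scale cannot be chosen with knowledge of the results.

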**Methods:**

To test our hypothesis, we are conducting a randomized, placebo-controlled clinical trial on 85 study participants who we stratify into two groups according to walking ability; those unable to walk (non-ambulatory group) and those able to walk (ambulatory group). The non-ambulatory group receives either daily AIH (15, 90s episodes at 10.0% O_2_ with 60s intervals at 20.9% O_2_) or daily SHAM (15, 90s episodes at 20.9% O_2_ with 60s intervals at 20.9% O_2_) intervention. The ambulatory group receives either 60-min walking practice (WALK), daily AIH + WALK, or daily SHAM+WALK intervention. Our primary outcome measures assess overground walking speed (10-Meter Walk Test), endurance (6-Minute Walk Test), and balance (Timed Up & Go Test). For safety, we also measure levels of pain, spasticity, systemic hypertension, and autonomic dysreflexia. We record outcome measures at baseline, days 5 and 10, and follow-ups at 1 week, 1 month, 6 months, and 12 months post-treatment.

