## Methods

### Study design and setting

We are conducting a double-blinded, placebo-controlled, counter-balanced, randomized phase II clinical trial to assess the effects of daily AIH, with or without walking practice, on walking function in persons with subacute SCI. We are conducting this study at the Spaulding Rehabilitation Hospital with institutional review board (IRB) approval from Partners Human Research Committee and IRB approval from the Shepherd Center (Atlanta, GA).

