**Fig. 1 Fig1:**
[figure not shown]
Timeline of intervention and outcome measurements

Participants receive 10 treatment sessions of daily AIH or daily SHAM. A single AIH session consists of 15, 90s episodes of breathing at a fraction of inspired oxygen (FiO_2_) of 0.10 ± 0.02 with 60s intervals of 0.21 ± 0.02 FiO_2_ (room air). While a single daily SHAM session consists of 15, 90s episodes of 0.21 ± 0.02 FiO_2_ with 60s intervals of 0.21 ± 0.02 FiO_2_ (room air). We provide the treatments via a custom air delivery system; see [10, 23, 32–34] for details. In brief, the delivery system directs a known air mixture from either a pressure-swing absorption (PSA) system [HYP-123; Hypoxico Inc., USA] or a blower source to the non-rebreather facemask. For safety, oxygen concentration within the breathing circuit is continuously monitored [OM-25RME; Maxtec Inc]. Additionally, we continuously monitor blood oxygen saturation (SpO_2_) and heart rate (HR) at 1-s intervals, and blood pressure (BP) every 5th breathing interval using a MASIMO system [MASIMO rainbow SET, Irvine, CA].
C.Walking practice

Walking practice sessions immediately follow (within 10 min) the breathing intervention and last for 60 min. Walking practice involves intensive training in walking-related functional tasks using a skill-based training approach. Recent studies found skill-based walking practice is more consistent with community walking, providing meaningful gains in walking function after neurologic injury [35–37]. Task-based walking practice replicates environmental challenges encountered during real-world walking [36] and corresponds to gains in walking balance, speed, and endurance that can be measured using the timed-up and go (TUG), 10-m walk test (10MWT), and 6-min walk test (6MWT), respectively [37]. The walking practice incorporates activities to develop skills in 5 walking-related task domains: 1) walking balance (e.g., walking on different surfaces), 2) skilled walking (e.g., negotiating obstacles), 3) walking with a secondary task (e.g., walking and carrying object), 4) endurance, and 5) speed [37].

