### Experimental protocol

D.Effects of dAIH on walking recovery in persons classified as non-ambulatory

We designed this protocol to examine if daily AIH improves walking recovery in persons with subacute SCI who are initially classified as non-ambulatory. Participants receive ten daily breathing sessions (5 days per week × 2 weeks) of either room air (daily SHAM) or daily AIH, while sitting comfortably in a chair or cushioned wheelchair. Each breathing session consists of 15 episodes of 90s hypoxia (0.10 ± 0.02 FiO_2_) for daily AIH or 90s normoxia (0.21 ± 0.02 FiO_2_; room air) for daily SHAM with 60s intervals of room air.
E.Effects of dAIH + WALK on walking recovery in persons classified as ambulatory

We designed this protocol to examine if daily AIH paired with task-specific, skilled, and intensive walking practice enhances walking recovery in persons with subacute SCI initially classified as ambulatory. Participants receive ten daily breathing sessions of either daily SHAM or daily AIH followed by daily 60-min walking practice (WALK). Our rationale is that daily AIH may be an effective pre-treatment for daily practice of walking skills, with the combined treatment being more powerful than either treatment alone, as seen in chronic SCI [10].

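### The double-blind label cannot cover the WALK arm, so AIH+WALK versus WALK should not carry the Aim 2 conclusion about AIH

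*Protocol article*

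**What the plan says.** Study design and setting describes a "double-blinded, placebo-controlled, counter-balanced, randomized phase II clinical trial" and names no exception.

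The Methods part of the Abstract gives three ambulatory arms: "The ambulatory group receives either 60-min walking practice (WALK), daily AIH + WALK, or daily SHAM+WALK intervention".

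Intervention, under Breathing treatment, knows only two kinds of breathing session: "Participants receive 10 treatment sessions of daily AIH or daily SHAM". Under Walking practice it adds: "Walking practice sessions immediately follow (within 10 min) the breathing intervention and last for 60 min". Experimental protocol describes the ambulatory participants in the same two-way form: "Participants receive ten daily breathing sessions of either daily SHAM or daily AIH followed by daily 60-min walking practice (WALK".

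Randomization and stratification has two sentences on masking. The first concerns participants: "Although we inform participants about their group, we blind them to the treatment they receive (i.e. daily AIH or daily SHAM"). The second concerns staff: "The clinical raters, trainers, and data analysts are also unaware of the treatment that each participant receives during after the trial".

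Statistical analysis, Hypothesis 2, names both comparators: "Daily AIH + WALK improves walking ability in ambulatory persons with subacute SCI as compared to daily SHAM+WALK and WALK". Sample size focuses the Aim 2 computation on AIH+WALK versus SHAM+WALK, but anticipates about 100 m more change in 6MWT distance against either SHAM+WALK or WALK.

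**The concern.** A participant allocated to WALK alone attends for practice and never wears the mask. No dummy procedure is described for that arm, so the participant knows the allocation from the first day. The trainer is likely to know as well. The trial-level label and the staff sentence admit no such exception.

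This matters because TUG, 10MWT and 6MWT are performed at the fastest speed that the participant finds comfortable, and so respond to effort and encouragement. The training therapist also adapts each practice session to the participant, so knowledge of the arm could affect the training itself. A difference between AIH+WALK and WALK may therefore reflect AIH, the experience of receiving a breathing treatment, added contact time, or training that was not quite the same. Only the sham comparison separates AIH from the rest. If the two comparisons count equally, Aim 2 could credit AIH with a difference that sham breathing would also have produced.

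**Working it through.** The point rests mainly on setting the statements side by side. The arithmetic only gives scale.

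**1. Does WALK have a breathing session?** The arms are WALK, AIH+WALK and SHAM+WALK. The only breathing treatments described are AIH and SHAM. If WALK participants breathed room air through the mask, WALK would be the same as SHAM+WALK. Since the two are separate arms, WALK has no breathing session. This is an inference from the arm structure; no sentence says it outright, and Table 2 and Fig. 1 are not shown.

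**2. Who is masked in each comparison?**

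| Comparison | Participants | Trainers | Raters and analysts |
|---|---|---|---|
| AIH versus SHAM | masked as stated | no walking practice | can be masked |
| AIH+WALK versus SHAM+WALK | masked as stated | can be masked | can be masked |
| AIH+WALK versus WALK | not masked | probably not masked | can be masked |
| SHAM+WALK versus WALK | not masked | probably not masked | can be masked |

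The entry for trainers in the last two rows rests on two statements. Practice starts within 10 minutes of the breathing session (Intervention), and the assigned physical therapist takes vital signs before and after both breathing and walking sessions (Safety precautions).

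**3. Extra session time.** Inputs: 15 episodes of 90 s, each with a 60 s interval (Intervention).
15 × (90 + 60) s = 2250 s = 37.5 min per day. This is added to 60 min of practice, so about 97.5 min against 60 min.

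**4. Share of Aim 2.** 51 / 3 = 17 participants in WALK, if allocation is equal (assumed).

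**5. Scale of a possible bias (illustration only).** The documents give no sham or expectation effect. Assume that AIH does nothing and that the WALK contrast carries a bias of b metres on the 6MWT. Inputs: SD 90 m and N = 51 with 12% attrition (Sample size). Then 51 × 0.88 = 44.88, or about 15 evaluable per arm. For an unadjusted two-sided 5% t-test, df = 2 × 15 − 2 = 28 and the noncentrality is (b / 90) × √(15 / 2).

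| Assumed bias b | Noncentrality | Probability of rejection |
|---|---|---|
| 0 m | 0 | 5% |
| 10 m | 0.30 | 6% |
| 20 m | 0.61 | 9% |
| 30 m | 0.91 | 14% |
| 50 m | 1.52 | 31% |

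A Tukey-Kramer adjustment would lower these figures. For AIH+WALK versus SHAM+WALK the corresponding figure stays at 5%, because both arms receive a breathing session. With the planned 100 m difference, the same calculation gives power of 0.836 for one unadjusted pair, so the sham contrast meets the stated power above 0.8 on its own.

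**The case against.** **Participant masking is already limited.** The sentence on participants confines it to AIH versus SHAM. This stands: that sentence is not false. What remains is the label in Study design and setting, which has no such limit.

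**The staff sentence can be read narrowly.** It follows directly on the sentence that explains treatment as AIH or SHAM, so it may mean only that staff do not know which of these was given. The reading is possible, but the text says each participant and makes no exception for WALK, so it needs clarifying either way.

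**Trainer unmasking is inferred.** Separate staff for breathing and practice are conceivable, and the table of Aim 2 groups is not shown. This stands, so the conclusion is that trainers probably know, not that they certainly do.

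**Raters and analysts.** A reader might infer that they are unmasked too, for instance because WALK participants have no breathing treatment to guess at the end of the day. The documents do not support this. Nothing says that the guess data reach raters or analysts together with the outcomes, and Data monitoring and management describes coded data and a masked lead therapist who checks scoring.

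**Hypothesis 2 names both comparators.** If AIH+WALK had to beat both, a bias against WALK alone could not make Aim 2 positive. That is correct, but the plan does not state this rule. It moves from a significant overall result to pairwise tests of all arms and does not rank them.

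**After treatment.** A reader might also infer that WALK participants would seek more outside gait rehabilitation once the two treatment weeks end. The rule on outside rehabilitation is the same for all arms, and nothing shows different behaviour.

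**Conclusion.** The point holds in a limited form. The unqualified double-blind label does not fit WALK. Participants in that arm know their allocation, trainers probably do, and AIH+WALK versus WALK cannot isolate AIH on effort-dependent tests. This affects one of the two contrasts in Hypothesis 2 and, with equal allocation assumed, 17 of 51 Aim 2 participants.

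It would be too strong to say that the trial, or Aim 2 as a whole, is unblinded. AIH versus SHAM in the non-ambulatory group and AIH+WALK versus SHAM+WALK are intact, and the latter is the stated focus of the Aim 2 sample size. It would also be too strong to claim a bias of known size: the 10 to 50 m range above is assumed. A third arm without sham is a legitimate design; the fault lies in how it is labelled and in the weight its contrast is given.

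The conclusion rests on WALK having no breathing session, which follows from the arms as described. The change should be made, because it determines what Aim 2 may claim for AIH.

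**What to change.** 1. In Study design and setting and in Randomization and stratification, restrict the blinding statements to AIH versus SHAM, with or without walking practice. Describe WALK as an open-label reference arm.
2. In the staff sentence, state who is masked to what. If trainers are kept unaware of WALK allocation, say how; otherwise exclude WALK from the claim about trainers.
3. In Hypothesis 2, base the conclusion about AIH on AIH+WALK versus SHAM+WALK, in line with the sample size.
4. Report AIH+WALK versus WALK as supportive. Report SHAM+WALK versus WALK, already among the Tukey-Kramer pairs, as the estimate of the sham and contact effect.
5. State that the analysis of treatment guesses covers only the arms with a breathing session.

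The cost is wording in the protocol and analysis plan. No further data or participants are needed and all three arms stay. The one loss is that a difference against WALK alone no longer supports the efficacy claim.
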